### Study outcomes and data collection methods

The primary and secondary outcomes were selected based on the hypothesized effects of the cognitive, physical, and psychosocial engagement components of choral singing. Table 2 lists specific components that were targeted during the choir intervention, their hypothesized links to the study outcomes, and the specific outcome measures assessed.

**Table 2 Tab2:** Components of community of voices intervention, hypothesized mechanisms of action, outcomes, and specific outcome measures

Component	Mechanism(s)	Outcomes	Specific outcome measures
COGNITIVE ENGAGEMENT			
Attend to conductor, music, and fellow singers; being flexible, organizing materials	Cognitive stimulation, brain	Attention/executive function	• *Trailmaking test*
			• NIH Toolbox Flanker
Learn and recall new music (lyrics, melody, pitch, and rhythm)	Cognitive stimulation, brain	Verbal learning and memory	• NIH Toolbox Rey Auditory Verbal Learning test
PHYSICAL ENGAGEMENT			
Stand and sit, move to rhythm of songs	Balance, body strengthening	Lower body strength, balance, falls	• *SPPB Chair stands*
			• NIH Toolbox Standing Balance
			• Self-reported falls
Stand and sit, move to different parts of room, breathe deeply to sing	Stamina	Walking speed	• NIH Toolbox Gait Speed
PSYCHOSOCIAL ENGAGEMENT			
Singing feels good, is uplifting, is intrinsically pleasurable and emotionally meaningful	Reduce depressive symptoms and anxiety, increase positive emotions	Emotional well-being	• PHQ-8
			• NIH Toolbox Sadness
			• NIH Toolbox Positive Affect
			• NIH Toolbox Fear Affect
Build social network, make new friends	Increase sense of belonging and social support, decrease feelings of loneliness	Social support, loneliness	• NIH Toolbox Loneliness
			• MOS Social Support
Somewhere to go, regular activity	Something interesting to do	Interest in daily life	• NIH Toolbox Apathy
Taking on new challenges, mastering new skills with practice over time	Improve sense of mastery, increase confidence	Self-efficacy	• NIH Toolbox Self-Efficacy

Primary outcomes are noted with italicized font; all other outcome measures are secondary

All primary and secondary outcomes were assessed at baseline, 6-months, and 12-months. For the convenience of participants, all assessments, including screening, took place at the senior center in which the person was enrolled. We collected data about falls and health care service utilization every three months either during the in-person assessments or by phone in between in-person assessments.

We used the National Institutes of Health (NIH) Assessment Center^SM^ as a platform to collect and manage all data (https://www.assessmentcenter.net). This is a free, secure, online data collection tool that provides real-time scoring of measures, automated accrual reports, and real-time data export. The Assessment Center enables researchers to create study-specific websites for capturing participant data securely online. Studies can include measures within the Assessment Center library such as the NIH Toolbox measures, as well as custom instruments entered by the researcher. We used the NIH Toolbox for the Assessment of Neurological and Behavioral Function [34] to assess many of the outcomes. The NIH Toolbox primarily uses a computer adapted testing (CAT) format based on item response theory (IRT); short-forms are also available which provide a fixed number of items. All NIH Toolbox measures are available in English and Spanish. We added several custom instruments that were not part of the Toolbox; all non-Toolbox measures were customized to be included as part of the Assessment center platform (e.g., format, randomization, skip patterns). All cognitive and physical function measures were performance based (e.g., required participants to perform a task such as walking or recalling words). All other measures were interviewer-administered. Below, we describe our primary and secondary outcomes including the rationale and specific measure used for each variable.

#### Primary outcomes

Our three primary outcomes include one from each of the hypothesized mechanisms of action of the intervention: cognitive, physical, and psychosocial engagement.

##### Cognitive engagement: attention/executive function

Attention and executive function refer to cognitive processes that require selective focusing, storing, and manipulation of information. We used two measures of attention/executive function, one of which was a primary outcome and one a secondary outcome. For the primary outcome measure, we used the Trail Making Test (TMT) [35, 36] which is a commonly used test of the set-shifting aspect of executive function. Studies involving music instrument training for older adults found improvement in executive function [37]. The TMT has been used as an outcome measure in clinical trials with community-dwelling older adults [38], including those from diverse and lower SES backgrounds [39, 40]. The TMT has two conditions: condition A requires participants to connect numbers in order as quickly as possible, while condition B requires participants to connect numbers and letters, alternating in order, as quickly as possible. Time to complete each condition is the variable of interest. We used Trails condition B minus Trails condition A (time) as an index of executive function because it isolates the executive control component of the TMT [41].

##### Physical engagement: lower body strength

Our primary outcome measure of physical engagement focused on lower body strength. We used the chair stands measure from the Short Physical Performance Battery (SPPB) [42] which is widely used for evaluating lower body strength in older adults. A previous study found that choral singing was associated with fewer falls [25], which may be related to improvement in lower body strength. Poor performance on the chair stands task is associated with poor health outcomes, such as functional decline, hospitalizations, and mortality [42, 43]. Chair stands have been used in several community-based clinical trials of older adults [44–47], some of which have included diverse individuals. The time to complete 5 chair stands was the primary variable of interest.

##### Psychosocial engagement: emotional well-being

We used several measures of emotional well-being, one of which was a primary outcome. The 8-item Patient Health Questionnaire (PHQ-8) [48] was used to assess depressive symptoms as the primary psychosocial outcome. In a previous study with a choir intervention for older adults, Cohen and colleagues found a trend for improvement in depressive symptoms [25]. The PHQ-8 asks participants to rate the frequency of depressive symptoms in the last two weeks including feeling depressed, having little interest in things, having trouble sleeping, being tired, having poor appetite, feeling bad about oneself, having trouble concentrating, and moving slowly. The PHQ-8 has good validity and reliability in diverse community samples [49, 50].

#### Secondary outcomes

All other outcome measures shown in Table 1 are secondary outcomes.

##### Cognitive engagement: attention/executive function

We used the NIH Toolbox Flanker Inhibitory Control and Attention Test as a secondary outcome measure of executive function. This measure taps both attention and inhibitory control. It is considered a “fluid ability,” assessing the capacity for new learning and information processing in novel situations. The test requires participants to focus on a given stimulus (a central arrow) when flanked by either congruent (same direction) or non-congruent (different direction) arrows. Participants complete 20 trials, and the final score reflects a combination of accuracy and reaction time over the 20 trials.

##### Cognitive engagement: verbal learning and memory

We used the NIH Toolbox Rey Auditory Verbal Learning Test as a secondary outcome of cognitive function. This is a word-list measure of “episodic memory” in which 15 unrelated words are presented orally (via audio recording) over three consecutive trials. After each presentation, participants were asked to recall as many words as possible. The measure is the sum of correct words for all three trials (range 0-45). We expanded this test to include two additional measures. After the three trials, participants listened to a (distractor) list of 15 new words and were asked to recall as many as they could (learning distractor list, score 0-15). Immediately after the distractor list, participants were asked to recall as many of the original 15 words as possible (short-term recall, score 0-15). The distractor and delayed recall conditions modifications were suggested by [name] (personal communication).

##### Physical engagement: balance and falls

As secondary outcome measures of physical engagement, we assessed balance and falls. The NIH Toolbox Standing Balance measure assesses static standing balance. Participants assume and maintain 5 poses. Four involve standing with their feet side-by-side (together) with these variations: eyes open on solid surface, eyes closed on solid surface, eyes open on foam surface, and eyes closed on foam surface. The fifth pose is to stand tandem (one foot aligned in front of the other) on a solid surface with eyes open. Participants were asked to hold each position for 50 s and postural sway is recorded for each pose using an accelerometer worn by the participant. Scoring involves their ability to hold the position for the time specified and the postural sway. We used the two scores recommended by the Assessment Center from these data: 1) ratio of poses 2/1 reflects the ability to use input from somatosensory and vestibular systems to maintain balance, and 2) ratio of poses 4/1 reflects the relative reduction in postural stability when visual and somatosensory inputs are simultaneously disrupted (typically representative of the effectiveness of vestibular function for postural control).

To measure falls, we assessed the frequency of falls over the past 3 months using a single question commonly used in several large studies about falls [51, 52]. The question was asked at 3-month intervals to obtain a complete assessment of falls over the 12 month period.

##### Physical engagement: walking speed

To assess walking speed, we selected the NIH Toolbox performance measure of gait speed which is a measure of “walking pace”. This is a timed walk in which participants were asked to walk 4 meters at their usual pace. They completed two timed trials with the score on the fastest trial considered as the outcome (meters per second).

##### Psychosocial engagement: emotional well-being

As secondary outcomes, we included 3 additional measures of emotional well-being. The NIH Toolbox Sadness CAT measure assesses the frequency in the past 7 days the individual felt, e.g., worthless, helpless, sad, depressed, unhappy, hopeless, had nothing to look forward to, and felt like a failure. The NIH Toolbox Positive Affect CAT measure assesses the frequency in the past 7 days the person felt, e.g., cheerful, attentive, delighted, happy, joyful, enthusiastic interested, peaceful, good natured, useful, understood, content, and liked oneself. The NIH Toolbox Fear/Affect Short Form measure assesses the frequency in the past 7 days the individual felt fearful, anxious, worried, nervous, uneasy, tense, and found it hard to focus.

##### Psychosocial engagement: social support and loneliness

To assess social support we selected six items from the Medical Outcomes Study (MOS) Social Support Survey [53]. Three items each were chosen from the Positive Social Interaction Scale and from the Emotional/Informational Support scale. Items assessed the extent to which respondents had someone to: have a good time with, get together with for relaxation, do something fun with, listen when you need to talk, give you advice if needed, and who understands your problems. We also administered the NIH Toolbox Loneliness Short Form measure which determines the frequency in the past month the person felt alone, apart from others, left out, lonely, and no longer felt close to anyone.

##### Psychosocial engagement: interest in daily life

We selected the NIH Toolbox Apathy Short Form measure to assess interest in life. This asks the frequency in the past month the person felt interested in things, got things done, saw a job through, got things started on one’s own, did interesting things, and was motivated.

##### Psychosocial engagement: self-efficacy

The NIH Toolbox Self-Efficacy Short Form measure assesses one’s confidence in handling problems.

### Measures of fidelity and compliance to choir intervention

The fidelity of the Community of Voices program across senior center sites, choir conductors, and styles of music was tracked using a 16-item survey with a 4-point scale. The fidelity survey focused on (i) implementation of the three key components of the choir program (cognitive, physical, and psychosocial engagement), (ii) leadership/communication skills, and (iii) musicianship. For each item, a score of 4 indicated that the performance of the conductor/accompanist exceeded program expectations; 3 indicated that the item met program expectations, 2 indicated that it was below expectations, and 1 indicated that it was not addressed and was well below expectations. The PI completed the fidelity check every three months, with an additional assessment three weeks after each choir began. Feedback was provided to conductors if the fidelity ratings on any of the 16 items fell below 3.

To assess compliance to the intervention, attendance was recorded at each choir session by the choir directors, and research staff coded absences according to the reason for the absence (e.g., illness, medical appointment, vacation, family issues).

### Intervention cost and cost effectiveness measures

In addition to evaluating the effectiveness of the intervention, we conducted cost-effectiveness analyses (CEA) of the program. As is commonly done for CEA, a single measure of health-related quality of life was used to measure the effect of the program. In addition, we determined the cost of the Community of Voices program, including the cost of the choirs themselves, in addition to any costs associated with changes in healthcare utilization on the part of the participants. The measures of cost and effectiveness are then combined into a measure of cost-effectiveness.

#### Health-related quality of life

Because of its widespread use in clinical trials and cost-effectiveness studies, we used the EuroQol Group’s EQ-5D (a brief multi-attribute, preference-based health status measure) [54, 55] to measure health-related quality of life. It has both English and Spanish versions and can be self- or telephone-administered by an interviewer. It covers five dimensions of health: mobility, self-care, usual activities, pain/discomfort, and anxiety/depression. These dimensions can be converted to a single index value by weighting each of the response levels, and this can be used to calculate quality-adjusted life years (QALYs) for the cost-effectiveness analysis. The scale has been used with diverse older adults in the US [56–58].

#### Costs

Costs included two components: the cost of the choir program and costs associated with differences in health care utilization. All costs will be converted to 2015 dollars using an appropriate price index for the cost component (e.g. the consumer price index for supplies, a wage index for salaries, and a medical cost index for healthcare costs).

#### Choir cost

For each choir, we collected all costs related to personnel (i.e., choir conductor and accompanist salaries), supplies (e.g., music binders, file box for music, piano purchase), and services (e.g., piano tuning). We also included the cost of providing snacks during the sessions.

#### Health care utilization

We tracked utilization of health care services using a modified measure from the Chronic Disease Self-Management study [59]. Every three months, we assessed visits to a doctor, mental health provider (e.g., counselor, psychologist), other health providers (e.g., home health nurse, physical therapist), emergency room visits and hospitalizations (including number of nights hospitalized and reason for stay), and outpatient surgeries over the past 3 months. The cost per unit of utilization (hospital days) was obtained from the Medical Expenditures Panel Survey and applied to the number of units used to obtain healthcare costs.

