To date, three longitudinal intervention studies of choral singing for older adults have been completed. Cohen and colleagues (2006) were the first to initiate a large-scale non-randomized study comparing 12 months of participation in a community choir for older adults to a usual activity comparison group. The choir met weekly for 33 weeks over a one-year period. At 12 months (85 % of those enrolled completed the 12 month assessment), those in the choir group reported higher self-rated health, fewer doctor visits, fewer over-the-counter medications, fewer falls, and less decline in morale and loneliness than the comparison group [25]. However, the groups were self-selected (recruited separately into the singing and comparison group), bias due to attrition was not considered, and the sample consisted predominately of non-Latino White women. Nonetheless, improvement in measures of several domains of health and well-being suggested better outcomes for the choir group, an important finding given the lack of prior studies. More recently, Coulton and colleagues completed a randomized controlled trial of a singing program for older adults in England [26]. Adults age 60 and older recruited from senior centers and nearby communities were randomized to a standardized singing program or a usual activity control group. The 90-min singing group met weekly for 14 weeks. There were significant differences between the intervention and control group after three months; participants in the singing group reported significantly higher scores on a mental health summary index and lower depression and anxiety, compared with the control group. Although the participants were randomized to the intervention and control groups, the sample was, again, primarily White women with high educational backgrounds. The outcomes focused only on mental health; thus the possible effects on other health aspects were not evaluated. The third study was a randomized controlled trial of a theater program for lower-income older adults that included a singing group as an active control condition, in addition to a usual-activity control group [27]. However, the authors did not report differences between the two control groups (e.g., between the usual activity group and the singing group). Within-group analyses indicated that the singing group improved on ratings of personal growth over the 4 weeks (p < .001). No other within-group changes were examined for significance.

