#### Cost-effectiveness analysis

The incremental cost-effectiveness ratio (ICER) is calculated as the difference in cost divided by the difference in QALYs for the immediate start choir group compared to the wait-list control group:$$ \mathrm{ICER}\kern0.5em  = \left({\mathrm{C}}_{\mathrm{i}}\kern0.5em \hbox{--} \kern0.75em {\mathrm{C}}_{\mathrm{c}}\right)\ /\ \left({\mathrm{E}}_{\mathrm{i}}\kern0.5em \hbox{--}\ {\mathrm{E}}_{\mathrm{c}}\right) $$

Where C = cost measured in dollars

E = effectiveness measured in QALYs

i = the intervention (immediate start choir) group

c = the wait-list control group

The ICER is the cost per QALY resulting from the program, and can be compared to other interventions. Interventions are typically considered to be reasonable if the cost per QALY is $50,000 - $100,000 or less.

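### The costing sentence names hospital days as the only priced unit, which does not match the declared scope of all health care use

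*Protocol article*

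**What the plan says.** Under Health care utilization, the article says that every three months "we assessed visits to a doctor, mental health provider (e.g., counselor, psychologist), other health providers", followed by "emergency room visits and hospitalizations (including number of nights hospitalized and reason for stay), and outpatient surgeries over the past 3 months". That makes six kinds of use. The next sentence gives the costing rule: "The cost per unit of utilization (hospital days) was obtained from the Medical Expenditures Panel Survey and applied to the number of units used".

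Two neighbouring sections say what the health care cost is meant to contain. Intervention cost and cost effectiveness measures includes "any costs associated with changes in healthcare utilization on the part of the participants". Costs defines the two components as "the cost of the choir program and costs associated with differences in health care utilization". Neither is limited to inpatient care.

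The section Cost-effectiveness analysis describes the ICER with the words "calculated as the difference in cost divided by the difference in QALYs for the immediate start choir group compared to the wait-list control group", and sets it against a benchmark of $50,000 to $100,000 per QALY. Study aims lists cost-effectiveness as the second of two main aims.

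**The concern.** The costing sentence is the only place where the article says how counts of use become dollars, and it names one unit. An analyst who followed it literally would price hospital stays and leave provider visits, emergency room visits and outpatient surgeries at zero. The result would not be the cost that the other two sections promise.

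The health care part of the cost difference goes straight into the ICER numerator. If the two arms differ in the unpriced categories, in either direction, the reported cost per QALY misses that difference. The one effect on utilization that the article cites lies in an unpriced category: members of the earlier choir study "reported higher self-rated health, fewer doctor visits, fewer over-the-counter medications, fewer falls" than its comparison group.

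**Working it through.** The article gives no unit costs, utilization rates, expected cost difference or expected QALY difference, so it has no cost figure of its own to reproduce. The check is mainly a comparison of texts.

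**1. What is collected and what is priced (Health care utilization)**

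| Category collected | Unit cost named in the costing sentence |
|---|---|
| Doctor visits | none |
| Mental health provider visits | none |
| Other health provider visits | none |
| Emergency room visits | none |
| Hospitalizations, with nights | hospital days |
| Outpatient surgeries | none |

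One of the six categories has a named unit and five do not.

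**2. Is the parenthesis an example or a definition?** The sentence just before it marks its examples with e.g. twice, and Choir cost uses both i.e. and e.g. The words on hospital days carry neither marker, so the literal reading is definitional. This supports that reading but does not prove it.

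**3. Comparison with the declared scope.** Both scope statements cover changes or differences in health care use without restriction. A rule that prices inpatient days alone yields a narrower quantity, so read literally the sections conflict.

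**4. Consequence for the ICER.** Write the true health care cost difference as H + O, where H is the hospital part and O is the part from the other five categories. Let P be the difference in program cost and E the QALY difference, taken as positive.

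- Full ICER = (P + H + O) / E
- ICER from hospital days only = (P + H) / E
- Shift from the omission = O / E

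If the choir lowers outpatient and emergency use (O below zero), the hospital-days version overstates the cost per QALY. If it raises such use, that version understates it.

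**5. Illustration with assumed values.** None of the inputs below is in the article. Take the absolute size of O as $50 to $300 per person and E as 0.005 to 0.03 QALY.

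- Smallest shift: 50 / 0.03 = about $1,700 per QALY
- A middle case: 100 / 0.01 = $10,000 per QALY
- Largest shift: 300 / 0.005 = $60,000 per QALY

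Against the $50,000 lower benchmark, these are about 3%, 20% and 120%. The omission could be negligible or decisive, and the article does not say which.

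**The case against.** The best defence is that the parenthesis loosely illustrates a unit. The sentence is otherwise generic, it follows directly on the full list of categories, and reading it as an example removes the conflict with the scope statements. An article may also leave a full table of unit costs to a document that is not shown. Part of this stands: that only hospital days are priced is the literal reading, not an established fact, and the lack of a per-category price list is no defect in an article. But condensing explains silence. It does not explain a sentence that names one unit at odds with two scope statements. If an example was meant, the sentence still describes the method wrongly and needs the same correction.

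Two stronger readings are tempting, and the article does not support either.

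- A reader might infer that the unpriced part is the one the choir is most likely to change. The article supports this for doctor visits only, from one non-randomized study that it criticises for self-selected groups and for not considering attrition bias. It cites no choir effect on mental health, emergency or surgery use, and it does not rank the categories. An effect on hospital use is not ruled out: the same study reported fewer falls, and the article links poor chair-stand performance to hospitalization.
- A reader might also argue that pricing hospital days alone leaves the cost difference dominated by a few long stays. That may be so, but the article gives no admission rates or costs from which to size it. Pricing the other categories would not cure it either, because hospital nights stay in the sum.

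It is also fair to say that the harm is limited. The three primary outcomes and their models are untouched, and the counts are collected, so nothing is lost yet.

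**Conclusion.** The point holds as an inconsistency within the article. The costing sentence, read as written, prices one of six collected categories, and this contradicts the scope in Intervention cost and cost effectiveness measures and in Costs. It affects the ICER numerator and hence the second main aim.

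The sign and size of the effect on the ICER cannot be determined from the article. The range of about $1,700 to $60,000 per QALY rests wholly on assumed values and shows only that the omission cannot be dismissed in advance. The conclusion rests on the literal reading of the parenthesis; if it was meant as an example, what remains is a wording error with the same remedy. The sections should be reconciled before the ICER is calculated.

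**What to change.** Replace the costing sentence with wording such as: *Unit costs (from the Medical Expenditures Panel Survey or another stated source) are applied to each category collected (doctor, mental health and other provider visits, emergency room visits, hospital nights, outpatient surgeries) and summed per participant.* The allowance for another source matters because the article does not say that the survey supplies a unit cost for every category.

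If pricing hospital days alone is intended, narrow the two scope statements to inpatient costs and say so wherever the ICER is reported.

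The cost is a change of wording and a few more unit costs. All the counts are already collected. The downside is that self-reported visits bring some recall error into the cost.
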